## Brain imaging parameters

The outcomes of brain imaging will evolve in three types of brain parameter types: (1) structural parameters of gray matter, (2) structural parameters of white matter fiber bundles, and (3) functional brain parameters of the brain at rest:With respect to the *structural parameters of gray matter*, they will encompass four main outcomes: thickness (THK), volume (VOL), surface area (SA), and gyrification (local gyrification index; LGI) across the entire brain.Within the *structural parameters of white matter fiber bundles*, we will evaluate the integrity of major white matter fiber tracts by measuring as a main outcome the fractional anisotropy (FA) and mean diffusivity (MD), aiming to elucidate the impact of BLT on these structural brain properties.Lastly, we will also evaluate the functional connectivity maps of specific brain networks (e.g., DMN, FPN, SN, and SMN) which are known to be impaired in depression. These functional connectivity maps are based on the blood-oxygenation level dependent (BOLD) signal under resting state conditions (resting state functional MRI).

Additionally, the pre- post-BLT assessment of these functional and structural brain networks will allow us to evaluate if the known functional and structural alterations of the brain in patients with depression changed after the BLT intervention. To evaluate the link between these biological markers and clinical symptom improvement, we will also look at the association between the earlier mentioned functional and structural brain changes and the change in depressive symptoms from pre- to post-BLT. This comprehensive and multiparametric (function and structure) MRI approach enables us to discern both structural and functional changes in the brain associated with the therapeutic effects of BLT.

## Light-related parameters

Personal light exposure will be evaluated using sensors developed by the Eindhoven University of Technology [88]. The light-related parameters for analysis may include logarithmic transformations of light level in lux illuminance (logEV) or melanopic equivalent daylight illuminance (mEDI) during specific periods, such as 1 h before EMA notifications, 3 h after waking, 3 h before bedtime, the interval between bedtime and wake time, and across the entire day. Time spent above certain light intensity thresholds (TaT), and the timing of these thresholds (mLiT) will also be examined. Key thresholds may include 5 lx at night, 1000 lx in the morning, and 250, 500, or 1000 lx during the day, as well as 100 lx in the evening. These parameters are flexible and can be adjusted as new research emerges. Light sensitivity will be estimated from the melatonin results, represented as the percentage decrease in melatonin production at specific time points during light exposure compared to the dim light condition, otherwise known as the light-induced melatonin suppression.

### Participant timeline {13}

The study unfolds in three distinct phases: the Baseline Phase, the Treatment Phase, and the Follow-up Phase. The following sections detail the specific procedures for each phase of the study. A schematic overview of the study procedures can be found in Fig. 2.

**Fig. 2 Fig2:**
[figure not shown]
This figure presents a schematic overview of the study design. The study is divided into three phases: Baseline, Treatment, and Follow-up. Participants receive Bright Light Therapy from Monday to Friday, with the option to repeat the treatment up to three times if the score on the Quick Inventory of Depressive Symptomatology – Self-report (QIDS-SR; [70]) remains higher than 6. Gray-colored areas in the figure represent optional parts of the study protocol. EMA; Ecological Momentary Assessment

### Baseline phase

In the Baseline Phase, participants undergo 1 to 2 weeks of measurements to assess their pre-treatment condition. The study begins with a 90-min face-to-face intake appointment (Intake). During this session, participants undergo the M.I.N.I. interview and complete the intake questionnaires. They also receive guidance on the proper use of the sensors and an explanation of how to use the BLT lamp. At the conclusion of the Intake, participants are randomized into one of the three treatment conditions.

One week before the start of therapy—typically on the following Monday—baseline examinations (B1) are conducted online. This includes completing the online questionnaires for B1 and a MADRS assessment via video call. Additionally, participants start with the EMA protocol and begin wearing the actigraphy watch and illuminance sensors. Those undergoing MRI assessments will also complete their baseline MRI scan (MRI-1) in the week before therapy. For participants involved in the melatonin assessments, an additional baseline week is added 2 weeks prior to the start of the treatment. This additional week includes the baseline DLMO assessment (M1) and an evaluation of light sensitivity (M2).

### Treatment phase

During the treatment phase, participants receive 1, 2, or 3 weeks of BLT within their assigned condition. Every Friday, depressive symptoms are assessed using the QIDS-SR, regardless of whether the participant received treatment that week. Treatment will be continued as long as QIDS-SR-score is higher than 6, with a maximum of 3 weeks. Treatment tolerability and mania symptoms are assessed using the YMRS after each week of BLT. EMA, actigraphy, and light logger usage continue throughout the treatment.

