### Eligibility criteria {10}

#### General eligibility criteria

Eligibility will be assessed during the intake by study team members trained in administering the MINI International Neuropsychiatric Interview 5.0.0 (M.I.N.I.; [69]). The inclusion criteria are as follows:Age between 18 and 65.Diagnosis of unipolar or bipolar depression (seasonal or non-seasonal) confirmed by the M.I.N.I. [69].Currently experiencing a depressive episode, as indicated by a Quick Inventory of Depressive Symptomatology Self-Report (QIDS-SR; [70]) score of 6 or higher.Proficiency in either Dutch or English is required for questionnaire completion.

Participants are excluded from participation if they:Are currently experiencing a (hypo)manic or mixed episode, as determined by the M.I.N.I. assessment [69].Are presently in a psychotic episode, as determined by the M.I.N.I. assessment [69].Exhibit significant active suicidality, indicated by a score of 10 or higher on the M.I.N.I. module [69].Initiated antidepressant therapy (including medication, psychotherapy, BLT, or other specific depression treatments) within the last 2 months prior to study enrolment.Have a bipolar disorder but are currently not under mood-stabilizing treatment for at least 1 month at the recommended dosage.Have used melatonin or agomelatine in the past month.Are currently using antibiotics.Are currently taking medications that increase light sensitivity.Have travelled across more than one time zone in the past month or during the treatment period.Have travelled to sunny holiday destinations or engaged in outdoor winter sports in the past month.Have pre-existing eye and skin disorders such as retinitis pigmentosa, porphyria, chronic actinic dermatitis, and sun-induced urticaria.Have systemic disorders with potential retinal involvement, such as rheumatoid arthritis and systemic lupus erythematosus.Have color blindness (based on self-report).Worked night shifts within the last three months.Suffer from (retinal) blindness, severe cataracts, or glaucoma.Experience light-induced migraine or epilepsy.Are currently pregnant or have a child Younger than 18 months old.

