### Intervention description {11a}

In all study arms, participants are subjected to BLT in adherence to Dutch BLT guidelines [72], utilizing an Innolux LED light Lamp delivering light with an illuminance of 10,000 lx at a distance of 70 cm and a color temperature of 3800 K. BLT sessions, lasting 30 min each, are scheduled from Monday to Friday between 7:30 AM and 10:30 AM.

The number of BLT sessions is contingent upon the individual response of each participant, with a maximum duration of 3 weeks. Initially, participants undergo five consecutive BLT sessions during the workweek. Subsequently, the therapeutic efficacy is evaluated utilizing the QIDS-SR during the Friday session. If the QIDS-SR falls below 6, remission is inferred, leading to the termination of BLT. Alternatively, an additional five sessions are administered. This evaluation and decision process is repeated at the end of the second week. If the QIDS-SR score is still above 6, a third and final week of treatment is provided.

This individualized strategy is intended to reduce the small risk of (hypo)manic switches, which occur in less than 2% of bipolar patients and almost exclusively in those not maintained on mood stabilizers [11, 73]. We will continuously monitor for (hypo)manic symptoms using the Young Mania Rating Scale (YMRS; [74]) and clinical observation: a YMRS score ≥ 13 and clinician‐identified symptoms will lead to immediate treatment cessation, while scores of 10–11 will prompt a joint review with a second clinician to decide on discontinuation [75, 76].

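### Neither the YMRS nor the Adverse Event Scale has a scheduled pre-treatment rating, so a raised score or complaint at the end of week 1 cannot be separated from symptoms present before light

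*Protocol article*

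**What the plan says.** **Screening.** General eligibility criteria: "Eligibility will be assessed during the intake by study team members trained in administering the MINI International Neuropsychiatric Interview 5.0.0". Patients are excluded if they "Are currently experiencing a (hypo)manic or mixed episode, as determined by the M.I.N.I. assessment". Table 1 marks the M.I.N.I. at Intake and nowhere else.

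**Time to treatment.** Baseline phase: "At the conclusion of the Intake, participants are randomized into one of the three treatment conditions". Then: "One week before the start of therapy—typically on the following Monday—baseline examinations (B1) are conducted online". Of that contact the article says "This includes completing the online questionnaires for B1 and a MADRS assessment via video call". For the melatonin participants "an additional baseline week is added 2 weeks prior to the start of the treatment".

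**Monitoring under treatment.** Treatment phase: "Treatment tolerability and mania symptoms are assessed using the YMRS after each week of BLT". Table 1 gives the YMRS and the Adverse Event Scale one mark each, under Evaluation. Their cells for Intake, B1, PT1, F1 and F2 are empty, and the table note says that a mark shows when an instrument is administered. Intervention description {11a} puts it differently: "We will continuously monitor for (hypo)manic symptoms using the Young Mania Rating Scale", together with clinical observation. It then sets YMRS bands on the absolute score.

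**The concern.** Both harms instruments start only after exposure. The M.I.N.I. at Intake yields a diagnosis of an episode, not a symptom score, so it gives no reference value for a later YMRS. No instrument marked at B1 rates mania or the side effects on the light-therapy checklist. Depression, by contrast, is measured at both Intake and B1 with the QIDS-SR.

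What is at stake is how harms are described. The article treats (hypo)manic switching as a risk that shapes the design, since the response-dependent length of treatment is meant to limit it. It also records headache, eyestrain and nausea as known effects of light. Such complaints and mild YMRS elevations can exist before any light is given. If the first rating comes after five sessions, a participant who already had the symptom looks the same as one who developed it.

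**Working it through.** The article prints no figure for the interval between the mania screen and treatment, so there is none to reproduce. It follows from the timetable by counting days.

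**Inputs**
- Intake falls on a weekday (assumption).
- The first baseline week starts on the following Monday. The Baseline phase section says this is typical for B1. For the melatonin subset I assume the extra week starts on that Monday instead.
- B1 to start of therapy is 7 days. The melatonin week adds 7 more (Baseline phase).
- Sessions run Monday to Friday, with the weekly evaluation on Friday (Intervention description {11a}). I take the first YMRS to fall on that Friday, 4 days after the start.

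**Formulas**
- Intake to first session = days to following Monday + 7 (+ 7 with melatonin)
- Intake to first YMRS = Intake to first session + 4

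| Intake day | Days to Monday | First session | First YMRS | First session, melatonin | First YMRS, melatonin |
|---|---|---|---|---|---|
| Mon | 7 | 14 | 18 | 21 | 25 |
| Tue | 6 | 13 | 17 | 20 | 24 |
| Wed | 5 | 12 | 16 | 19 | 23 |
| Thu | 4 | 11 | 15 | 18 | 22 |
| Fri | 3 | 10 | 14 | 17 | 21 |

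So the only scheduled mania assessment is typically 10–14 days old at first light, and 17–21 days old in the melatonin subset. That subset is 72/231 = 31% of the planned sample, so the shorter interval applies to about 69%. The first YMRS comes 14–18 or 21–25 days after Intake. A B1 later than the following Monday would lengthen all of these.

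**What the schedule allows one to conclude**
- *Is the score above a cut-off now?* Yes. The bands in Intervention description {11a} are absolute and need no baseline.
- *Do arms differ at week 1?* Yes, in expectation. Randomization balances symptoms present at Intake, and a baseline would mainly add precision.
- *Is this participant's symptom new since light began?* No. There is no earlier value on either instrument.

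**How often this matters** cannot be computed. The article cites switches in less than 2% of bipolar patients. It gives no spontaneous rate for the pre-treatment weeks, no expected bipolar share and no background rate of headache or eyestrain.

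**The case against.** The strongest reply is that nothing specified depends on a baseline. The YMRS serves as a check against fixed cut-offs. Adverse events are defined without regard to their relation to light and are also recorded when reported spontaneously or observed. The article's statistical sections name no change score for either instrument. All of this stands, and it limits the point to the attribution of symptoms.

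Three stronger readings are tempting but not supported.

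- *A reader might infer that patients start light unscreened for mania.* The supported statement is that no mania assessment is scheduled between Intake and the first week's evaluation. Bipolar patients must already be on mood-stabilizing treatment. Clinical observation is named, and staff may stop treatment on clinical assessment. Each LightCafé session includes a 5–10 min consultation with a nurse or psychologist, LightCafé+ begins with a study-team call, and personal contact is maintained throughout. None of these is a scheduled rating, and less contact is described for Light@Home, so unscheduled detection may differ by arm.
- *A reader might infer that the comparison of harms between arms is lost.* It is not, because allocation is randomized.
- *A reader might infer that the sections contradict each other on when monitoring begins.* Intervention description {11a} gives no start time, and weekly ratings plus ongoing observation is a fair reading of it. This is a wording point only.

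The reply does not remove the empty cells. The schedule is printed in full in Table 1, so this is not detail lost in condensing a protocol into an article.

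**Conclusion.** The point holds as a gap in measurement. The YMRS and the Adverse Event Scale have no pre-treatment value, and the first rating follows five sessions. Participant-level statements that a symptom emerged under treatment, and any count built on them, therefore lack a reference.

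The interval of 10–14 days, or 17–21 with melatonin sampling, rests on a weekday Intake and the typical following-Monday start. The number of symptoms that would be misclassified is unknown. No claim that misclassified cases would rival the expected number of switches can be supported, because the article gives no denominator for it.

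A baseline also has limits. It separates symptoms already present from those new since baseline. It does not prove that light caused the new ones, since every arm receives light. Because allocation is open and made at Intake, the value would be pre-treatment but not pre-randomization.

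The primary efficacy analysis is unaffected. This is a low-cost improvement to the assessment schedule.

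**What to change.** 1. In Table 1, add the Adverse Event Scale to the B1 online questionnaires.
2. In Table 1 and the Baseline phase section, add one YMRS before the first session. It should be given by trained unblinded study staff and not by the blinded MADRS rater, whose blinding to arm and time point should not be put at risk.
3. Report treatment-emergent YMRS elevations and side effects relative to these values. Keep every randomized participant in the intention-to-treat set, since randomization takes place at Intake, before this rating.
4. Align the description of continuous monitoring in Intervention description {11a} with the weekly schedule in the Treatment phase section and Table 1, separating scheduled ratings from clinical observation.

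Whether and how the (hypo)mania exclusion is verified again, and what follows from a raised pre-treatment score, is for the sponsor to set.

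**Cost.** Two instruments already in use, a few minutes per participant, and possibly one brief extra contact in Light@Home. The Trial status section says enrolment began in February 2024, so the change can only reach participants not yet treated. For the others, week-1 findings should be reported as present at week 1 and not as emergent.

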### Follow-up phase

After the treatment has been completed, EMA, actigraphy, and light logger usage are extended for an additional week and are discontinued on the Sunday at the end of this additional week. The post-treatment DLMO assessment (M3) and MRI scan (MRI-2) also occur within this first week after BLT.

Following these assessments, a post-treatment evaluation (PT1) is scheduled 4 weeks after the start of treatment, which includes a series of online questionnaires and an online MADRS assessment. During this meeting, participants receive general insights into their EMA data. The online follow-up questionnaires (F1) are sent 10 weeks after the start of treatment, with the second set of follow-up questionnaires (F2) distributed 4 months after the start of treatment, after which study participation is discontinued.

### Sample size {14}

#### Justification for the complete sample size

The sample size for this study was determined based on the power needed to answer our primary objective. A power analysis was initially conducted using G*Power 3.1 [89] to evaluate a simplified statistical approach comparing the MADRS scores across three treatment conditions using repeated measures ANOVA. This analysis was based on a clinically relevant effect size of *f* = 0.25, a significance level (α) of 0.05, and a desired power (1 − β) of 0.90, assuming a non-sphericity correction of 1. The results indicated that a total sample size of 210 participants would be necessary to detect significant differences.

To further validate this sample size, a simulated dataset was constructed using the R package *simr*, comprising 210 participants, each assigned to one of the three treatment conditions. The initial depression scores were set to a mean of 23.4 (*SD* = 13.2) based on research by Müller et al. [90]. Effect sizes of the treatment conditions were set to − 0.25, − 0.33, and − 0.4 corresponding to *Light@Home, LightCafé* and *LightCafé* + respectively, reflecting low to medium effect sizes. A power simulation of a linear mixed model using depression scores as the dependent variable, treatment condition and time point as fixed effects (including their interaction), and a random intercept per participant, revealed that the model achieved a high power of 98.30% (95% CI 97.29, 99.01) to detect significant interactions between time points and treatment conditions at an alpha level of 0.05, based on 1000 simulations. Assuming a drop-out rate of approximately 10%, we aim to include 231 participants in our trial.

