### Concealment mechanism {16b}

A randomization table was generated using ResearchManager before the start of the trial. Access to the randomization table is restricted for the whole research team and can only be accessed by an independent researcher of the Eindhoven University of Technology not affiliated with the study. The randomization process in ResearchManager employs permuted block randomization with blocks of six to maintain balanced allocation across study groups.

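### The simulated 98.30% power for the primary arm-by-time test does not follow from the stated arm effects, so it does not validate N = 210

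*Protocol article*

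**What the plan says.** The sample size is argued in two steps in the protocol article, under Sample size {14}, Justification for the complete sample size.

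- **G*Power step.** A repeated-measures ANOVA comparing three arms, with f = 0.25, alpha 0.05 and power 0.90, gives 210 participants.
- **Simulation step, offered as further validation.** The simulated data set is described as "comprising 210 participants, each assigned to one of the three treatment conditions". For the outcome: "The initial depression scores were set to a mean of 23.4 (*SD* = 13.2". For the arms: "Effect sizes of the treatment conditions were set to − 0.25, − 0.33, and − 0.4", assigned in order to Light@Home, LightCafé and LightCafé+, and described as "reflecting low to medium effect sizes". The model has "treatment condition and time point as fixed effects (including their interaction), and a random intercept per participant". The result is that it "revealed that the model achieved a high power of 98.30% (95% CI 97.29, 99.01) to detect significant interactions between time points and treatment conditions".

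The section on the primary study outcome makes the same interaction, on pre- and post-treatment MADRS, the primary analysis. Table 1 schedules the MADRS at B1 and PT1 only. The article gives no pre-post correlation, no residual SD and no units for the three effect sizes.

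**The concern.** An arm-by-time interaction responds only to differences between arms in their change. Three effects of -0.25, -0.33 and -0.40 are nearly alike, so they carry little signal for that test, however large the average improvement. Yet the simulation reports higher power (98.3%) than the G*Power step (90%) at the same N, for arm differences that look much smaller than f = 0.25.

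This is the power statement for the primary objective. If it is wrong, readers will think the trial almost certain to detect differences of the size the authors simulated. A null result could then be taken as strong evidence that the café setting and personalised timing add nothing.

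**Working it through.** **Inputs.** N = 210, baseline mean 23.4, SD 13.2 and arm effects 0.25, 0.33, 0.40 come from the sample-size section. Two time points come from the primary-outcome section and Table 1. Equal arms of 70 are inferred from "permuted block randomization with blocks of six to maintain balanced allocation across study groups". The pre-post correlation ρ is not stated and is varied here as an assumption.

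**What reproduces.**
- The reported interval is the exact binomial interval for 983 of 1000 runs (97.29% to 99.01%), so the simulation output is reported consistently.
- N = 210 reproduces when f is on the scale of the change score: λ = f²(N − 3) = 0.0625 × 207 = 12.94, and noncentral F with df 2, 207 gives power 0.902. The article does not say which G*Power effect-size option was used; this one returns 210.
- For three equally spaced arms, f = 0.25 is a gap between the extreme arms of 0.25 / 0.408 ≈ 0.61 SD of change.

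**The interaction power.** Read the effects as pre-post change in units of SD 13.2.
- Differences between arms: 0.08, 0.07 and 0.15 SD, or 1.06, 0.92 and 1.98 MADRS points.
- Mean effect 0.3267; variance (0.005878 + 0.000011 + 0.005378) / 3 = 0.003756; f = 0.061 on the baseline SD.
- With two time points and a random intercept, the interaction test is a one-way F test on change scores, whose variance is 2(1 − ρ) in squared SD units. So λ = 210 × 0.003756 / [2(1 − ρ)], with df 2, 207. The residual SD is 13.2 × √(1 − ρ).

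| Assumed ρ | Residual SD (points) | λ | Power |
|---|---|---|---|
| 0 | 13.2 | 0.39 | 8.0% |
| 0.3 | 11.0 | 0.56 | 9.4% |
| 0.5 | 9.3 | 0.79 | 11.3% |
| 0.7 | 7.2 | 1.31 | 15.9% |
| 0.8 | 5.9 | 1.97 | 22.0% |
| 0.9 | 4.2 | 3.94 | 40.5% |
| 0.95 | 3.0 | 7.89 | 70.4% |
| 0.98 | 1.9 | 19.7 | 98.3% |

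A direct simulation of 4000 runs gave 11.4% at ρ = 0.5 and 22.2% at 0.8. Power of 98.3% needs λ = 19.78, hence 1 − ρ = 0.7887 / (2 × 19.78) = 0.0199, ρ ≈ 0.98 and a residual SD of 1.86 points.

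**Consistency of the two steps.** On the change-score scale the stated effects have f = 0.061 / √[2(1 − ρ)]: 0.061 at ρ = 0.5, 0.097 at 0.8, 0.137 at 0.9. They reach 0.25 only when 2(1 − ρ) = 0.003756 / 0.0625 = 0.060, that is ρ ≈ 0.97. Below that, the simulated scenario is weaker than f = 0.25 and must have less than about 90% power at N = 210.

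**Other analyses under the same reading.** The largest pairwise contrast has 14% power at ρ = 0.5 and 29% at 0.8. Baseline adjustment gives 13.6% and 24.1%.

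**Other readings of the effect sizes.**
- *Percentage reductions of the mean 23.4.* Effects scale by 23.4 / 13.2 = 1.773, so f = 0.109. Power is 27% at ρ = 0.5 and 59% at 0.8; 98.3% needs ρ ≈ 0.937.
- *Raw MADRS points.* Power is about 5%.
- *-0.33 and -0.40 as interaction coefficients against the control.* Differences 0, 0.33, 0.40 give f = 0.174. Power is 61% at ρ = 0.5, 95% at 0.8, and 98.3% at about 0.84.
- *Per-step slopes over four time points.* Power is 98.4% at ρ = 0.8.

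**The case against.** The strongest reply is that the article does not report enough to prove any particular power. Correlation, residual SD and units are all missing, and 13.2 might be only the between-person SD, since the companion DLMO simulation in the same section lists between- and within-person SDs separately. This stands in part. A reader might infer that the true power is 11-22%, but that range depends on assumed correlations of 0.5 to 0.8 and on one reading of the units. It does not rescue the printed figure: if 13.2 is the between-person SD, effects in units of 13.2 still need a residual SD of 1.86 points on a 0-60 scale.

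Two readings do reach about 98% at less extreme correlations. The interaction-coefficient reading conflicts with the text, which gives Light@Home its own effect of -0.25; it would imply total changes of -0.58 and -0.65 in the café arms. The per-step reading needs more MADRS assessments than the two scheduled. If either was simulated, the section misdescribes it and still needs correcting.

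A reader might also infer that the authors tested the wrong term, because the pooled time effect has 97.9% power at ρ = 0.3 and 99.7% at 0.5. That is possible, but nothing in the article shows it.

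Nor do the documents support the inference that N is wrong. The simulation is presented as a check on N = 210, and the G*Power step stands without it. The drop-out step, "Assuming a drop-out rate of approximately 10%, we aim to include 231 participants in our trial", is 210 × 1.10. A 10% loss from 231 leaves 208, with power for f = 0.25 still 89.9%, and a 9.1% loss leaves exactly 210. With the rate given only as approximate, this is not a defect worth raising.

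**Conclusion.** The 98.30% figure is not supported by the inputs printed with it and should not stand as validation of the sample size. Under the most natural reading, interaction power at N = 210 is about 11% at an assumed pre-post correlation of 0.5, 22% at 0.8 and 40% at 0.9. The exact value is unknown because it depends on quantities the article does not state. The conclusion is firmer than any single value: no reading consistent with one effect per arm and two MADRS assessments reaches 98.3% below a correlation of about 0.94, and the most natural one needs about 0.98.

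N = 210 is adequate for f = 0.25 on the change-score scale, with about 90% power. It is not shown to be adequate for the smaller arm differences that the authors simulated. The calculation assumes equal arms, complete pre and post MADRS data and a two-sided 5% level.

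**What to change.** - Withdraw the 98.30% statement. Alternatively, rerun the simulation and restate the result with the model coefficients, their units, the residual SD or pre-post correlation, and the exact term and test evaluated.
- State that N = 210 gives 90% power for f = 0.25 only, about 0.6 SD of change between the extreme arms, and name the G*Power effect-size option used.
- Report the power for the stated arm effects over an explicit range of correlations, labelled as assumptions: about 11% at 0.5, 22% at 0.8 and 40% at 0.9 if the effects are in baseline SD units.

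The cost is a rewritten paragraph and, if chosen, a short rerun. Enrolment, randomisation and the analysis model are unaffected, and no extra patients are needed. The downside is that the published power becomes far less favourable for the effects the authors described.
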